## Statistical analysis

### Statistical Analysis for Study Objective 1.

We will analyze “Reach” as the percentage of PLWH who participated in the screening for tobacco use for each facility and compare between the control and implementation group using chi-square test. We will examine sociodemographic and clinical characteristics of smokers who did not participate. As analysis of primary outcome with intention-to-treat, the clinical effectiveness endpoint will be compared between the control group and implementation group at the individual level with a generalized linear mixed model with a binary distribution using the jack-knife method to estimate standard errors to account for grouping within clusters and by incorporating a log-link function to estimate the relative risk as a measure of effect. We will include random effects to account for the clustering within facilities and periods and fixed effects for type of facilities. The model will be selected as the best model with unique covariance structure that produces the lowest Bayesian Information Criterion (BIC) value. The covariance structures that will be considered in the model are the first order of autocorrelation covariance structure, unstructured covariance structure, and Toeplitz covariance structure. We will use the Satterthwaite method to adjust for denominator degree of freedom for the test for fixed effects. The random coefficients will be modeled using G-side random effects, and we will obtain the subject-specific estimates by defining the appropriate variance-covariance structures.

Sex-stratified and age-stratified analyses and models will be performed as secondary analyses. Given high quality of data and experience in conducting studies in Botswana, we do not expect to have missing observations in the variables required for the primary analysis. To address the concern about contamination, we will conduct a sensitivity analysis excluding patients in the control group in the 90 days before crossing over to the implementation group. Because there will be fewer than 50 clusters, we will conduct a sensitivity analysis using a small sample correction with the Kenward-Roger method.

As analysis of secondary outcomes at 6 months, 30-day point prevalence abstinence will be compared between the implementation and the control groups in a similar model to the one used in the analysis of the primary outcome. Longitudinal differences in the Stages of Change Algorithm between the implementation and the control groups will be compared using random-mixed effect regression. Analysis will be conducted to assess factors associated with completion of varenicline regimen using generalized estimating equation model for binary repeated measures.

## Statistical analysis for Study Objective 2

The CFIR will be used to guide qualitative interviews and activity log coding analysis. The CFIR-ERIC Matching Tool, which provides a menu of 39 constructs across five domains (Intervention Characteristics, Inner Setting, Outer Setting, Characteristics of Individuals, and Process), will be used to generate a list of potential strategies to address implementation barriers.

Qualitative data analysis. The CFIR will provide the structure for the initial codebook to guide qualitative data and activity log data using a descriptive content coding approach. The coding approach will be both deductive (codes derived from CFIR constructs) and inductive (codes derived from the data). During the coding and rating phases of analysis, the analysts will be blinded to the implementation effectiveness. Data will be independently coded by a revolving team of two analysts. Codes will be compared, and differences will be resolved by consensus discussion.

Quantification of qualitative data. We will quantify qualitative data and activity log data by having two analysts independently assign ratings for each code to reflect its positive or negative impact on implementation. Ratings will range from -2 to +2 with 0 to reflect a neutral or mixed influence of the code. For each facility, data will be consolidated, and two analysts will independently rate each code across all the interviews to obtain a facility rating for each time period. This process will be repeated for the two rounds of interviews and monthly for activity logs.

Quantitative measure of implementation success. Implementation effectiveness will be assessed by measuring the extent of integration of BSMART into the clinical setting within participating facilities. Therefore, we will focus on **Adoption** which will be analyzed monthly and for the 12 months of implementation as the number of clinic days per month LHW case managers delivered SBIRT divided by the number of operating clinic days per month. **Implementation with fidelity** will be analyzed monthly and for the 12 months of implementation period as the number of SBIRT provided with repeated intervention over time by LHW case managers to PLWH who smoked divided by the number of PLWH who are eligible for the program. Pearson's correlation will be used to assess the strength of correlation between qualitatively derived construct ratings from qualitative interviews and activity logs, and implementation effectiveness across facilities.

### Statistical Analysis for Study Objective 3

RE-AIM measures will be re-assessed at 24 months after BSMART implementation to provide a standardized evaluation approach to foster understanding of whether the impact and implementation delivery are maintained and to shed light on where sustainability issues arise e.g. which clinic and population the implementation is not reaching. Trends in the outcomes of clinical effectiveness (collected and analyzed in Study Objective 1) and implementation effectiveness (collected and analyzed in Study Objective 2) will be compared between the implementation period and the maintenance period using chi-square test.

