## Methods

### Study Design

We will utilize a stepped wedge cluster randomized trial to implement BSMART. BSMART will be sequentially rolled out to 15 participating HIV treatment and care facilities assigned in three steps (Table 1). Each step will provide data for a 12-month control/pre-implementation, a 12-month implementation, and a 12-month maintenance period. We will stratify Botswana's HIV treatment and care facilities into three levels of facilities. We will randomly assign each of the three levels of facilities to one of three study steps. Each step will comprise (i.e. have representation) from three levels of facilities, giving each level of facilities the same probability of beginning the intervention at any step). We choose this design to:

- 1) minimize the practical, logistical, and financial constraints associated with large-scale project implementation,
- 2) control for the effect of time, and
- 3) ensure that all HIV treatment and care practices will eventually offer the intervention and assess maintenance.

The study will screen approximately 6,900 HIV-infected patients and we expect to enroll 750 eligible participants, 375 of whom will participate in the pre-implementation phase and 375 of whom will participate in the implementation phase across three waves of implementation at five facilities each.

| Table 1: Time Periods for Stepped Wedge Implementation |                                                  |         |                |                |                |             |
|--------------------------------------------------------|--------------------------------------------------|---------|----------------|----------------|----------------|-------------|
| Steps                                                  | Total Number of Participants                     | Year 1  | Year 2         | Year 3         | Year 4         | Year 5      |
| 1                                                      | 5 facilities, n=250 PLWH (1DH, 2 PHs, 2 clinics) | Control | Implementation | Maintenance    |                |             |
| 2                                                      | 5 facilities, n=250 PLWH (1DH, 2 PHs, 2 clinics) |         | Control        | Implementation | Maintenance    |             |
| 3                                                      | 5 facilities, n=250 PLWH (1DH, 2 PHs, 2 clinics) |         |                | Control        | Implementation | Maintenance |

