## Study Population

Participants will be drawn from the population of HIV-infected patients receiving care at 15 selected health facilities that are part of the Accelerating Botswana through the Last Mile to Epidemic Control (ABLE) project. We plan to screen approximately 6,900 HIV-infected patients (230 PLWH per facility per year) for tobacco smoking and subsequently identify 750 patients who are interested in quitting into the trial, a total of 375 of whom will participate in the control period and 375 of whom will participate in the implementation period across three waves of implementation at five facilities each. Study participants will receive HIV care and treatment according to national standards.

Eligibility criteria: To maximize “real world” practice we attempted to err on the side of inclusivity in the study’s eligibility criteria. We will apply the following inclusion criteria:

- (1) HIV-infected,
- (2) self-reported current daily smoker,
- (3) age 18 years and older,
- (4) engaged in HIV care as defined by being on ART for at least 6 months at one of 15 selected health facilities (or four reserve facilities), and
- (5) willing/able to provide informed consent in English or Setswana.

We will apply the following exclusion criterion:

- (1) pregnancy or nursing

We acknowledge that patients living with HIV/AIDS in real-world treatment settings use other substances in addition to tobacco and will often have some problems associated with that use. To limit this study to those who smoke tobacco only means tailoring the intervention to a small group that is not truly representative of the larger population of PLWH.

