##### Semi-structured Interviews

During their final study visit at week 24, participants will be asked to participate in a semi-structured interview. For participants who were unable to quit smoking in the course of their participation in the study, the reasons for this will be explored. For participants who quit and resumed smoking, the factors that prevented them from staying smoke free will be explored. For participants who were successful in quitting, the factors that enabled them to quit successfully will be identified.

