### 2. Measures to assess the Adoption and Implementation of SBIRT

- Activity Logs: During the implementation period, implementation leaders and care teams will be sent a monthly email requesting that they complete an activity log, which will take 15–30 minutes to complete depending on the number of activities to report. The logs will collect information about implementation activities, intent, duration, and individuals involved. We will ask them to take an inclusive approach and include any activities they believe are related to implementation. We will also add a hypothetical example to the instructions and share a list of discrete implementation strategies. Each month, the research team will invest up to two hours to collect and combine the logs then follow-up with implementation leaders at sites to address their questions.
- Scripts from Focus Group discussions with LHWs
- Responses from SSIs
- SBIRT checklists

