**Fig 6: ICER**

unit change in the 7-day point prevalence abstinence at 6 months, comparing between the implementation and control groups. Net benefit (NB) regression provides an appropriate approach to quantify the ICER using the incremental net monetary benefit (INMB) and produce a confidence interval around the ICER.

In equation 1 of Figure 7 we define NB as the difference between the monetized total effect measure (the product of lambda, the willingness to pay per unit of effect, and the total effect units available, e) and the associated costs. The NB regression model is specified in equation 2 of Figure 7 as the difference between effects and costs, estimated via a parametric regression framework where errors are represented by the final term in equation 2, epsilon. Alternative formulations of equation 2 include a generalized linear regression model that incorporates a skewed distribution of the NB. We will identify the initial value of lambda following a targeted literature review and consultations with onsite study collaborators. In equation 2 of Figure 5, the NMB, represented by the  $\beta$  coefficient on the indicator variable for receipt of intervention (i.e., 'Implementation'), will be estimated using the NB regression model.

$$NB_{ij} = (\lambda - e_{ij}) - c_{ij} \dots \dots \dots (1)$$

$$NB_{ij} = \beta_0 + \beta_1 \times \text{implementation}_{ij} + \epsilon_{ij} \dots \dots \dots (2)$$

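### Reach and net benefit are compared between phases with no facility or calendar-time term, and the implementation-versus-maintenance comparison has no data collection scheduled on the maintenance side

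*Protocol*

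**What the plan says.** **Reach.** Statistical Analysis for Study Objective 1 defines Reach as the percentage of PLWH who took part in screening, for each facility, and will "compare between the control and implementation group using chi-square test". The primary outcome in the same section gets a mixed model: "We will include random effects to account for the clustering within facilities and periods and fixed effects for type of facilities".

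**Net benefit.** Under Objective 4, equation 2 contains an intercept, an implementation indicator and an error term. It is "estimated via a parametric regression framework where errors are represented by the final term in equation 2, epsilon". The only alternative named is a generalized linear model for skewness.

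**Maintenance.** Under Objective 3, trends in clinical and implementation effectiveness "will be compared between the implementation period and the maintenance period using chi-square test".

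**Design.** "BSMART will be sequentially rolled out to 15 participating HIV treatment and care facilities assigned in three steps". Table 1 gives each step a control year, then an implementation year, then a maintenance year, with steps starting in Years 1, 2 and 3. Controlling for the effect of time is one of three stated reasons for the design. Screening is planned at "230 PLWH per facility per year", about 6,900 in all. Enrolment is 375 in control and 375 in implementation.

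**The concern.** In a stepped wedge each facility's treated year comes later than its control year, so a plain before-after comparison mixes the intervention with whatever else changed in that year. A two-group chi-square and equation 2 make exactly that comparison. They also ignore that outcomes within a facility are correlated and that a facility's level may shift from year to year. The protocol allows for clustering in the primary model but not here, so the Reach and cost-effectiveness conclusions could owe something to calendar time or to facility-level drift.

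The maintenance comparison raises a different problem. A test needs observations on both sides, and the schedules appear to supply only one. Maintenance-year data that are not collected cannot be recovered at analysis.

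**Working it through.** **1. The plan's own figure.** The only related figure is the 87% power for the primary endpoint (10% versus 20%, 25 per cluster-period, ICC 0.02, 5% loss). With m = 25 × 0.95 = 23.75, the design effect is 1 + 22.75 × 0.02 = 1.455. The effective number per phase is 15 × 23.75 / 1.455 = 244.8, and power is 87.5% at two-sided alpha 0.05 (assumed; the value is not printed). The figure reproduces and is not in dispute. No power or sample size is given for Reach, net benefit or maintenance.

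**2. Calendar time.** Assume no intervention effect, stable facility effects, Reach near 80% and 15 × 230 = 3,450 people per phase. The standard error of the difference is √(2 × 0.8 × 0.2 / 3,450) = 0.0096.
- Trend of 1 point per year: z shift 0.010 / 0.0096 = 1.04; rejection at 5% about 18%.
- Trend of 2 points per year: z shift 2.08; rejection about 55%.

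Simulation (20,000 runs) gave 17% and 55%. A paired facility-level t test still rejected in 16% and 50%, so handling facility alone does not remove the trend. The same confounding applies to equation 2, but its size cannot be computed because no net-benefit variance or willingness-to-pay value is given.

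**3. Clustering without a trend.** Let r be the correlation of a facility's effect between its two years (assumed). With each facility in both phases, the true variance of the pooled difference over the variance chi-square uses is

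ratio = (1 − ICC) + m × ICC × (1 − r), and type I error = 2 × [1 − Φ(1.96 / √ratio)].

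At ICC 0.02 and m = 230:
- r = 1: 0.98, type I error 4.8%
- r = 0.9: 0.98 + 0.46 = 1.44, 10%
- r = 0.5: 0.98 + 2.30 = 3.28, 28%

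At m = 25 (net benefit) the ratio is 0.98 at r = 1 and 0.98 + 0.25 = 1.23 at r = 0.5.

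**4. Price of adjusting for year.** Each step has one control and one implementation year, so the three within-facility differences cannot separate three year-to-year changes from the effect. With fixed years, the estimate leans on between-facility contrasts in Years 2 and 3, five facilities against five in each. The generalized least squares variance for this layout, with four year terms and a phase term, relative to the chi-square variance:

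| m | ICC | r = 1 | r = 0.9 | r = 0.5 |
|---|---|---|---|---|
| 230 | 0.02 | 4.9 | 5.3 | 6.7 |
| 230 | 0.05 (assumed) | 10.1 | 10.9 | 14.4 |
| 25 | 0.02 | 1.8 | 1.9 | 2.0 |
| 25 | 0.05 (assumed) | 2.4 | 2.5 | 2.8 |

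**5. What is scheduled for maintenance.**
- Participants: 15 × 2 × 25 = 750, all in control or implementation; none is left over.
- Screening: 15 × 2 × 230 = 6,900, two years per facility.
- Follow-up: the Semi-structured Interviews section refers to participants "During their final study visit at week 24".
- Activity logs: "During the implementation period, implementation leaders and care teams will be sent a monthly email requesting that they complete an activity log"; the Process Variables table also limits them to the intervention phase.
- Adoption and fidelity: defined monthly and for the 12 implementation months.
- Recruitment: the timeline table marks none in Year 5, which is Step 3's maintenance year.
- The Program Sustainability Assessment Tool (PSAT) is the only process tool listed for the maintenance phase.

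**The case against.** Several points on the other side stand.

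- A reader might infer that chi-square must be too liberal. It need not be: each facility is its own control, a constant facility effect cancels, and the test is then slightly conservative. Inflation needs facility-by-year variation, whose size the documents do not give.
- The 230 per facility-year is the number to be screened, not the Reach denominator, which is not stated. It serves here only as a stand-in. The ICC of 0.02 was stated for abstinence.
- If the words on each facility mean 15 separate tests, between-facility clustering drops out. Calendar time and facility-by-year variation remain.
- A reader might infer that the protocol declares net-benefit errors independent. It does not; that is read from an equation with no facility or period term, and standard errors could be specified elsewhere. The cost-effectiveness aim is also labelled preliminary.
- A reader might infer that Objective 3 can have no maintenance data at all. The documents do not support that. Study Design says each step provides maintenance data, RE-AIM measures are to be re-assessed at 24 months, the Study timeline plans maintenance analysis at patient and facility level, and its follow-up row runs to the end of Year 5. The 5 A's form is built into clinic intake, so delivery records might exist without study logs. But no maintenance-phase collection of that form, or any enrolment, CO or questionnaire visit, is stated. Late implementation enrollees may reach week 24 in the maintenance year, but they were treated under implementation.

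An unseen SAP does not settle the matter: the protocol itself fixes the chi-square tests and equation 2, and an SAP cannot analyse data that nobody is scheduled to collect.

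**Conclusion.** The point holds in three parts of different strength.

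1. **Calendar time, firm.** The Reach and net-benefit contrasts are unadjusted before-after comparisons in a design chosen to control for time. The 18% and 55% false-positive rates rest on the assumed trend, Reach level and number per phase; the confounding itself does not.
2. **Clustering, conditional.** For Reach, type I error runs from about 5% to 28% over r = 1 to 0.5 at ICC 0.02 with the stand-in of 230. For net benefit, the variance ratio of 0.98 to 1.23 is minor.
3. **Maintenance, an internal inconsistency.** Data are promised in several places and scheduled in none, apart from the PSAT. This is an unscheduled promise, not proof that no data will exist.

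The primary-endpoint analysis is not touched by this point.

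**What to change.** **Reach and net benefit.** Replace the Reach chi-square with a mixed model, and extend equation 2, using random facility and facility-by-period effects and fixed terms for calendar year and facility type. Write the calendar-year term in explicitly: the primary model as worded has fixed effects only for facility type, so referring to it would not bring in a fixed year adjustment. State the Reach denominator. The cost is precision: over ICC 0.02 to 0.05, variance is about 5 to 14 times the chi-square value for Reach and about 2 to 3 times for net benefit. The protocol should say so, so that a wide interval is not read as evidence of no effect.

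**Maintenance.** Continue the monthly activity log and the 5 A's checklist through each site's maintenance year, extend the adoption and fidelity definitions to it, and compare them in a facility-month mixed model in place of chi-square. The log takes 15 to 30 minutes a month, for 12 more months per site. For clinical effectiveness, reconcile the sections: either state which people, visits and measurements supply the maintenance-period data, or restrict the comparison to the implementation measures. The first option adds data collection; the second narrows a stated objective.

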The Parliament of Botswana had in August 2021, passed a Tobacco Control Bill, which is currently awaiting signature by the President of Botswana. This Bill, which is sponsored by the Minister of Health and Wellness aims to discourage smoking initiation, encourage quitting, and reduce tobacco consumption overall to address prevention and control of non-communicable diseases such as lung cancer. The Global Adult Tobacco Survey conducted in 2017 shows that while the majority of smokers in Botswana made an attempt to quit in the past 12 months, only 7% of smokers were able to successfully quit. The Government of Botswana wants more to be done to assist its citizens in smoking cessation.

The average years of life lost by PLWH smokers compared with HIV-positive non-smokers have been estimated as 12.3 years, which is more than twice the number of years lost by HIV infection alone. Botswana is particularly vulnerable because of its near transition from a Stage 1 tobacco smoking epidemic (prevalence of cigarette smoking <20%) to a Stage 2 (rapid increase in male smoking and prevalence beyond 20%). It is expected to face the largest growth in tobacco consumption in the world. If interventions for PLWH can be designed and implemented at scale, a significant impact on lung cancer control can be achieved.

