## Power and Sample size

Our sample size is based on the hypothesis that interventions will have a substantial impact on primary endpoints compared to the control phase (Figure 5).

**Main effect:** Based on a meta-analysis of 24 randomized controlled trials in LMIC, smoking abstinence at 6 months follow-up ( $P_{\text{control}}$ ) for usual care averages 10% (range, 8% to 14%). Assuming withdrawal from trial follow-up or loss to follow-up to be 5%, our sample of 25 PLWH per cluster per period has power of 87% to detect at least 10% increase (main effect,  $\Delta = (P_{\text{implementation}} - P_{\text{control}})$ ) in the primary endpoint at six months with the assumption that the event rate for those in control phase is 10% and two-sided alpha at intra-cluster correlation of 0.02.

[figure not shown]

Fig 5. Power to detect primary endpoint, main effect versus standard of care (SOC)

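### The primary model treats period only as a random effect although implementation always falls one calendar year after control, so it does not deliver the control for time that the design promises

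*Protocol*

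**What the plan says.** The section Statistical Analysis for Study Objective 1 specifies a generalized linear mixed model with a log link, jack-knife standard errors and Satterthwaite degrees of freedom. On its terms it says: "We will include random effects to account for the clustering within facilities and periods and fixed effects for type of facilities". The covariance candidates are the "first order of autocorrelation covariance structure, unstructured covariance structure, and Toeplitz covariance structure", chosen by lowest BIC. Two sensitivity analyses are named: one excludes control patients from the 90 days before crossover, and one uses the Kenward-Roger correction. Neither adds a time term. The secondary outcome of 30-day abstinence is to use a similar model.

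Under Study Design, "Each step will provide data for a 12-month control/pre-implementation, a 12-month implementation, and a 12-month maintenance period". Table 1 places step 1 in Years 1 and 2 (control, then implementation), step 2 in Years 2 and 3, and step 3 in Years 3 and 4. One of the three reasons given for the design is to "control for the effect of time".

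**The concern.** Randomisation decides when a facility starts, not the order of its two conditions: implementation follows control everywhere. Without an estimated mean for each calendar period, the intervention estimate is an average before-after difference within facilities, and national change in quitting over the same years is mixed into it. That is what a stepped wedge is meant to prevent, and what this protocol says it chose the design to prevent.

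The protocol itself gives grounds to expect change, in either direction. The Background says: "The Parliament of Botswana had in August 2021, passed a Tobacco Control Bill, which is currently awaiting signature by the President of Botswana", and describes the Bill as meant to encourage quitting. The same section expects Botswana to see very large growth in tobacco consumption. At stake is the primary estimate of the primary endpoint, and neither planned sensitivity analysis would show the problem.

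**Working it through.** **Inputs.** 15 facilities, 5 per step (Study Design); 25 participants per facility per period, 5% loss, so 23.75 analysed; control rate 10%, implementation rate 20%; intra-cluster correlation 0.02 (Power and Sample size). The facility-by-phase cells number 15 × 2 = 30, and 30 × 25 = 750. Assumed, because not given: alpha 0.05; cluster autocorrelation (persistence of a facility's effect from one year to the next) 0 to 1; secular trend 1 to 3 points per year. Calculations are by generalized least squares on the risk-difference scale, as a stand-in for the log-link model, with the correlation treated as known.

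**The protocol's own figure.** It states "our sample of 25 PLWH per cluster per period has power of 87" per cent for 10% against 20%.
- Design effect: 1 + (23.75 − 1) × 0.02 = 1.455.
- Effective number per condition: 15 × 23.75 / 1.455 = 244.8.
- SE: √(2 × 0.15 × 0.85 / 244.8) = 0.0323.
- Power: Φ(0.10/0.0323 − 1.96) = Φ(1.14) = 87%.

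This contains no time adjustment. A complete stepped wedge with fixed period effects also gives 87.0%, but it needs 15 × 4 = 60 cells, or 1,500 participants. The protocol does not say which calculation was used.

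**Bias without fixed period effects.** Let μ1 to μ4 be the shared yearly levels. With facility or facility-by-period random effects, the estimate is the mean within-facility difference, so its bias is

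[(μ2 − μ1) + (μ3 − μ2) + (μ4 − μ3)] / 3 = (μ4 − μ1) / 3.

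A linear trend of d points per year gives 3d/3 = d. A single 3-point jump at Year 3 gives 3/3 = 1 point. Mean year is (1+2+3)/3 = 2 for control and (2+3+4)/3 = 3 for implementation.

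**Bias if period is one random year effect shared by all facilities.** The year effect is shrunk, so part of the trend remains. The share that enters the estimate, over overall abstinence of 10-15% and autocorrelation 0 to 1, is:

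| Year SD (points) | Share of trend in estimate |
|---|---|
| 1 | 94-97% |
| 2 | 80-88% |
| 5 | 40-54% |

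**Bias with fixed year effects.** Zero. Years 2 and 3 each hold implementation facilities from one step and control facilities from another, so the year effects are estimable.

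**False-positive rate with no true effect and no fixed year effects.** Rejection = Φ(d/SE − 1.96) + Φ(−d/SE − 1.96). The upper column holds variance at 10% abstinence with autocorrelation 1: SE = √(2 × 0.98 × 0.09 / 23.75 / 15) = 0.0223. The lower column uses autocorrelation 0 and the mean abstinence that the trend implies (11.5%, 13%, 14.5%): SE 0.0288, 0.0304, 0.0318.

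| Trend (points/year) | Lower | Upper |
|---|---|---|
| 1 | 6.4% | 7.3% |
| 2 | 10.1% | 14.6% |
| 3 | 15.6% (15.3% at a mean of 15%) | 27.1% |

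A binomial simulation with a facility random effect gave 7.4%, 12.5% and 20.1%, against 4.6-5.6% when year was fixed.

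**Power with fixed year effects, 30 cells.** At autocorrelation 0 the information comes only from Years 2 and 3. Cell variance is 0.1275 × 1.455 / 23.75 = 0.00781. Each year's contrast compares 5 cells with 5, and two years are averaged: variance (2 × 0.00781 / 5) / 2 = 0.00156, SE 0.0395.

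| Autocorrelation | SE | Power, 10 points |
|---|---|---|
| 1 | 0.0362 | 79% |
| 0.5 | 0.0379 | 75% |
| 0 | 0.0395 | 72% |

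For the 8-point effect named in the Rationale, the same SEs give 53-60%. With variance taken at 10% against 18% (mean 14%; SE 0.0384 to 0.0351) the figures are 55-62%. Without year effects the 30 cells give 87-97% for 10 points.

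**The case against.** The strongest reply is that the sentence on model terms is not a full list: it does not name the intervention effect either, and a separate analysis plan could add terms. That would carry weight if the protocol were silent on period. It is not. It assigns period to the random part and names facility type as the fixed part, and the covariance structures describe correlation, not calendar means. Citing stepped-wedge methods papers does not supply a time term.

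Other points stand and limit the claim. A reader might infer that period is ignored altogether, or that every secular change passes in full into the estimate. The documents do not support that: period is in the model as a clustering effect, and under a shared random year effect only part of a trend enters. A reader might also infer that the bias must favour BSMART. The Bill is described as awaiting signature, with no date of effect, and the expected growth in tobacco consumption could push the other way. No document gives a trend in quitting; 2 to 3 points a year is a large relative change on a 10% base, and at 1 point a year the false-positive rate moves little. The upper false-positive figures also hold variance at 10% abstinence and use a normal test, although the protocol specifies Satterthwaite degrees of freedom, so they sit at the high end.

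**Conclusion.** The point holds. As written, the primary model does not control for time, although that is a stated reason for the design. The share of a shared linear trend that enters the estimate is all of it under facility or facility-by-period random effects, and about 40-97% under a shared random year effect, depending on the year variance. The direction is unknown. False-positive rates of roughly 6-7%, 10-15% and 15-27% are conditional on assumed trends of 1, 2 and 3 points a year; they show sensitivity and do not predict this trial's error rate. The bias result follows from Table 1 alone. The size of the power loss rests on alpha 0.05, the stated correlation of 0.02, an unknown autocorrelation and the linear-scale approximation. Because this concerns the primary analysis of the primary endpoint, it should be corrected before outcome data are seen.

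**What to change.** Add calendar period as a categorical fixed effect to the primary model, beside phase and facility type, and to the similar model for 30-day abstinence. Keep random facility and facility-by-period effects. Show the model without fixed period effects only as a sensitivity analysis.

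Under Table 1 the factor has four yearly levels. The Study timeline chart instead marks three recruitment blocks (Year 1 Q4 to Year 2 Q2, Year 2 Q4 to Year 3 Q2, Year 3 Q4 to Year 4 Q2). The two schedules need reconciling first, and the levels should follow the result.

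The wording change is small, but the cost is real. With 750 participants, power for 10% against 20% becomes about 72-79% rather than 87%, and about 53-62% for the 8-point effect. The Power and Sample size section should be restated with the time-adjusted model, saying which effect size and autocorrelation it assumes. Choosing the covariance structure by BIC is a separate, secondary matter: no choice among those structures replaces the missing period means.
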